**Table 2- Measures and testing schedule**

| Measure |  | 0 wk | 6 wk | 10 wk |
| --- | --- | --- | --- | --- |
| RRV & liking of activity | 1^O^ outcome | X | X | X |
| Usual physical activity | 2^O^ outcome | X | X | X |
| Body composition | 2^O^ outcome | X | X |  |
| Aerobic fitness | 2^O^ outcome | X | X | X |
| Muscular pain | 2^O^ outcome | X | X | X |
| Dietary intake | 2^O^ outcome | X | X | X |
| Questionnaires |  |  |  |  |
| Self-efficacy | 2^O^ outcome | X | X | X |
| Affect during exercise | 2^O^ outcome | X | X | X |
| Social norm of exercise | 2^O^ outcome | X | X | X |
| Tolerance of discomfort | 2^O^ outcome | X | X | X |
| Psychological needs satisfaction | 2^O^ outcome | X | X | X |
| Behavioral regulation in exercise | 2^O^ outcome | X | X | X |
| Perceived autonomy support | 2^O^ outcome |  | X |  |

**Physical activity reinforcement task and liking of physical activity:** The RRV_PA_ assessed by evaluating the number of responses (mouse button presses) a participant is willing to complete to gain access to a PA or alternative sedentary reinforce [[41](#_ENREF_41), [42](#_ENREF_42)]. Just as a rat will lever press to receive a chow pellet, people will press a button to get access to behavioral alternatives. For a rat, the number of presses required to obtain the food reinforcer can be increased over time to determine the reinforcing value of food. Food is more reinforcing for rats that are willing to press a greater number of times to receive the food. For humans, the procedure begins by determining the liking of the physical activity and sedentary alternatives using a 10-point Likert-type scale (1 = “do not like at all” and 10 = “like very much”) and choosing the highest rated PA for the testing session. A sedentary alternative is included so that the subjects are not responding for exercise out of boredom (there is nothing else to do). The lab space includes two workstations. One station is a computer and mouse on which the participant can earn points towards their highest liked physical activity (e.g., treadmill, cycle ergometer, elliptical step ergometer). At the other station is a computer to earn points towards the highest liked sedentary alternative (reading magazines, paper-pencil puzzles). Participants can switch between stations as much as they choose. The program presents a game that mimics a slot machine. A point is earned each time that the shapes match. For every 3 points, the subject will receive 2 min of access to reinforcer that was earned. At first, points are delivered after every 4 presses, but then doubles (8, 16, 32, […] 1024) each time 3 points are earned. For instance, the participant initially has to click the mouse 4 times to earn each point, but after the first 3 points and reward is earned, then 8 clicks are required to earn each of the 3 points, and so on [[41](#_ENREF_41), [42](#_ENREF_42)]. Participants will engage in each alternative reinforcer for the time earned at the end of the session.

**Physical activity***.* Physical activity duration and energy expenditure during each treatment session and during free-living physical activity will be measured using a SenseWear Mini® [[43](#_ENREF_43)] or Computer Science and Applciations (CSA) monitor.

**Body composition.** Height and weight will be measured and BMI calculated. Body composition will be assessed with total body DXA (iDXA, GE Lunar).

**Aerobic fitness***.* Subjects will complete submaximal fitness tests on a motorized treadmill. Given the sedentary nature of the participants, the test will be stopped when the subject reports a rating of perceived exertion (RPE) of > 7, achieves a HR associated with 85% of predicted % heart rate reserve (%HRR), or 3) a respiratory exchange ratio of 1.0. These parameters allow sedentary subjects to exceed VT by 2 or more stages so that VT can be determined [[44](#_ENREF_44)]. Heart rate measured via telemetry from a chest band (Polar Electro Inc., Lake Success, NY) and metabolic data via indirect calorimetry (TrueOne 2400, ParvoMedics, Sandy UT) will be continuously monitored. VT will be determined from plots of the ventilatory equivalent for oxygen (V_E_/VO_2_) and the ventilatory equivalent for carbon dioxide (V_E_/VCO_2_) versus time. VT is identified as the workload before V_E_/VO_2_ begins to increase without an increase in the V_E_/VCO_2_. The HR and workload corresponding to VT will be determined for the test of affect during exercise and for physical activity prescription. Beat-to-beat blood pressure stroke volume, total peripheral resistance, cardiac output, and pulse rate variability will be monitored continuously during the exercise test using a finger cuff and infrared plethysmograph (Finometer PRO, Finapres Medical Systems, Amsterdam).

**Feeling Scale (FS)**. The FS (APPENDIX 15) [[45](#_ENREF_45)] is a single-item measure of affective valence and ranges from -5 to +5 with descriptive anchors at 0 (neutral) and all odd integers, anchored by “Very Bad” [[46](#_ENREF_46)] to “Very Good” (+5) [[45](#_ENREF_45)]. The Feeling Scale has a moderate to strong correlation (0.51 to 0.88) with the Valence scale of the Self-Assessment Manikin [[47](#_ENREF_47)] and from 0.41 to 0.59 with the Valence scale of the Affect Grid [[48](#_ENREF_48)].

**Felt Arousal Scale (FAS)**. The FAS (APPENDIX 16) [[38](#_ENREF_38)] is a six-point, single-item measure of perceived activation that ranges from 1 to 6 with anchors of “Low Arousal” and “High Arousal” [[38](#_ENREF_38)]. The FAS correlates with the Arousal scale of the SAM ranging from 0.45 to 0.70 and with the Arousal scale of the AG from 0.47 to 0.65 [[47](#_ENREF_47)].

**Perceived Exertion**.

Borg’s Rating of Perceived Exertion (RPE) scale (APPENDIX 17) will be used to measure perceived effort [[39](#_ENREF_39)] during the affect-during-exercise treadmill test at the same time points as the FS and FAS (above) as a measure of perceived exercise intensity. The weighted mean validity coefficients for Borg’s RPE scale are 0.62 for heart rate, 0.57 for blood lactate, 0.64 for %VO2max 0.63 for VO2, 0.61 for ventilation and 0.72 for respiration rate [[49](#_ENREF_49)].

**Muscular pain***.* Pain intensity of the whole body, shoulders and legs will be measured at rest, each stage of the fitness test, during cool down, and 10 min after the test using the muscular pain scale modeled after Borg’s category-10 ratio scale (APPENDIX 18) [[50](#_ENREF_50)]. Muscular pain and exertion will be measured at the same time points as the FAS, FS, and RPE scale during the affect-during-exercise treadmill test [[51](#_ENREF_51)].

Figure 1. Circumplex model

**Activation Deactivation Adjective Check List (ADCL)**

[figure not shown]
The AD ACL [[40](#_ENREF_40)] is a multi-item scale that measures the affective dimensions of Energetic Arousal (EA) and Tense Arousal (TA) and will be administered pre and post exercise. The AD ACL (APPENDIX 19) consists of 20 self-descriptive adjectives of Energy, Tiredness, Tension, and Calmness. The AD ACL is scored by assigning 4, 3, 2, and 1, respectively to the "√√,√, ?" and "no" scale points, and summing the five scores for each adjective. In order of appearance, the adjectives are as follows: Energetic (active, energetic, vigorous, lively, full-of-pep); Tired (sleepy, tired, drowsy, wide-awake, wakeful); Tension (jittery, intense, fearful, clutched-up, tense); Calmness (placid, calm, at-rest, still, quiet). Scoring for "wakeful" and "wide-awake" must be reversed for the Tiredness adjective. Tiredness and Tension scores must be reversed (but not wakeful and wide-awake in this case) before summing the ten scores. The FS, FAS, and AD ACL will be displayed from the perspective of the circumplex model. As shown in **Figure 1**, the energy pole (high EA) maps the high-activation pleasure quadrant. Tension (high TA) maps the high activation displeasure quadrant. Tiredness (low EA) maps the low-activation displeasure quadrant, and calmness (low TA) maps the low-activation pleasure quadrant [[40](#_ENREF_40), [52](#_ENREF_52)]. Subjects will complete the AD ACL immediately before, after, and 10 minutes after the affect-during-exercise treadmill test. Values from the FS, FAS, and AD ACL will be calculated seperatly at each time point and plotted on the circumplex model to display changes in affect throughout the exercise bout and pre-post exercise [[53](#_ENREF_53)].

**Tolerance for the discomfort of exercise***.* The Preference for and Tolerance of the Intensity of Exercise Questionnaire (APPENDIX 6) [[30](#_ENREF_30), [31](#_ENREF_31)], and the Discomfort Intolerance Scale [[32](#_ENREF_32)] (APPENDIX 7) will be completed. These measures will be tested as predictors of RRV_exercise_ as both preference and tolerance are related to the frequency of participation in strenuous exercise and the total leisure-time exercise [[30](#_ENREF_30)].

**Self-efficacy for exercise***.* Self-Efficacy will be assessed using the Exercise Self-Efficacy Scale (EXSE, Appendix 4) [[35](#_ENREF_35)] and the Exercise Confidence Survey (Appendix 9) [[54](#_ENREF_54)] The EXSE assesses an individual’s beliefs in their ability to continue to exercise at moderate intensity for 40 or more minutes per session, 3 times/wk.  Participants score each item on a 100-point scale ranging from 0% (not at all confident) to 100% (highly confident).  For the Exercise Confidence Survey participants rate how confident they are that they could really motivate her/himself to do things related to trying to increase or continue regular exercise, for at least six months. Participants score each item on a 5-point scale ranging from 1 (I know I cannot) to 5 (I know I can).

**Social norms and support for exercise***.* Social norms will be measured using subjective and descriptive norm items (APPENDIX 8) [[33](#_ENREF_33)]. Social support will be assessed using the Social Support and Exercise Survey [[34](#_ENREF_34)] which tests both family and friend participation in exercise with the subject. Participants first rate how often anyone in their family and then how often their friends have said or done various aspects related to social norms and support of exercise. Participants score each item on a scale ranging from 1 (none) to 5 (very often).

**Psychological Need Satisfaction in Exercise (PNSE).** The PNSE is an 18-item self-report questionnaire that assesses respondents’ perceptions of competence, autonomy, and relatedness felt during exercise (APPENDIX 11) [[55](#_ENREF_55)]. Each item is scored on a 6-point Likert scale (1 = not at all true… 6 = very true) in terms of how they feel while exercising. The PNSE has excellent structural and convergent validity and internal consistency of 0.90 to 0.91 for each of the competence, autonomy, and relatedness subscales in physically active young adults [[55](#_ENREF_55)].

**Behavioral Regulation in Exercise Questionnaire (BREQ).** The BREQ is a 15-item self-report measure that assesses external, identified, intrinsic, and introjected regulations (APPENDIX 12) [[56](#_ENREF_56)]. Each item is scored on a 5-point scale ranging from 0 (not true for me) to 4 (very true for me). Validity of the BREQ’s four-factor structure, the gender invariance of that factor structure, and the internal consistency (0.76 to 0.90) of the subscales has been established [[56](#_ENREF_56)].

**Sport Climate Questionnaire.** Perceived autonomy support from the coach/trainer is measured using the short (6 items) version of the Sport Climate Questionnaire (APPENDIX 21). The original scale [[57](#_ENREF_57)] that assesses perceptions of autonomy support provided by a health care provider was revised by the original authors such that the term ‘‘my health care provider’’ was replaced with ‘‘my exercise class leader’’. Moreover, participants respond to the items in reference to the first 2 weeks of exercise sessions monitored by GFHNRC staff. Each item is scored on a 7-point scale ranging from 1 (strongly disagree) to 7 (strongly agree). The original questionnaire [[57](#_ENREF_57)] has a one-factor solution that measures perceived autonomy support and internal consistency of 0.95.

**Dietary intake***.* The Automated Self-Administered 24-Hour Dietary Recall (ASA24) will be used to collect dietary information. Subjects will report dietary information for 3 weekdays and 1 weekend day each testing period. The ASA24 is based on the multi-pass method [[58](#_ENREF_58)] and has been shown to effectively assess mean energy intake within 10% actual intake [[59](#_ENREF_59)].

**Expectations***.* Subject outcome responses to a treatment may be influenced by the expectations that they have before starting treatment. Treatment expectations of the study will be assessed with the Stanford Expectations of Treatment Scale (SETS) tailored for the current study (APPENDIX 14). The SETS tool assesses expectancy effects that can be covaried for in the statistical analyses. Treatment expectations will be assessed at baseline.

**Goals***.* After the subjects have completed the 6 weeks of treatment, they will be asked to detail any new exercise or sports participation goals they have made since beginning study participation.

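### The AD ACL scoring rule reverses Tension where it should reverse Calmness, so Tense Arousal runs opposite to the protocol's own definition

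*Protocol*

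**What the plan says.** The Activation Deactivation Adjective Check List (AD ACL) is described in the Protocol under C. Methods, iv. Measures. According to that section it "measures the affective dimensions of Energetic Arousal (EA) and Tense Arousal (TA"). There are four five-adjective subscales: Energy, Tiredness, Tension and Calmness. The two that matter here are "Tension (jittery, intense, fearful, clutched-up, tense") and "Calmness (placid, calm, at-rest, still, quiet"). Responses run from a double check mark down to no and are scored 4, 3, 2 and 1.

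For the ten-item sums the rule is: "Tiredness and Tension scores must be reversed (but not wakeful and wide-awake in this case) before summing the ten scores". Calmness is not mentioned, so it enters as scored.

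The section then fixes the direction of each dimension against the circumplex figure. For Energetic Arousal (EA), "the energy pole (high EA) maps the high-activation pleasure quadrant", and tiredness is its low end. For Tense Arousal (TA), "Tension (high TA) maps the high activation displeasure quadrant", and "calmness (low TA) maps the low-activation pleasure quadrant".

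The AD ACL is completed before, immediately after and 10 minutes after the affect treadmill test, and its values are plotted on the circumplex. Table 2 lists affect during exercise as a secondary outcome.

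**The concern.** A bipolar score takes the direction of the pole that is left unreversed. For EA the protocol reverses the low pole (Tiredness) and leaves the high pole (Energy) alone, so EA rises with energy as defined. For TA it does the opposite: it reverses the high pole (Tension) and leaves the low pole (Calmness) alone. The result is a score that rises with calmness but carries a name and a definition saying that it rises with tension.

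Direction is what this measure contributes. The Background argues from opponent-process theory that repeated exposure turns initial anxiety about exercise into eagerness and improves affect after exercise. A mirrored TA score read under the protocol's labels would show falling tension as rising tension, and so appear to contradict that theory when the data support it. A tense participant placed on the circumplex by this score would sit at the calm pole.

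**Working it through.** **Inputs, all from the AD ACL section of the Protocol**

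- Item scores: 4, 3, 2, 1, taken as higher meaning more of the adjective. A reversed item is therefore 5 − x.
- Five items per subscale: each raw sum runs from 5 to 20, and a reversed subscale is 5 × 5 − sum = 25 − sum.
- Stated poles: energy is high EA, tiredness low EA, tension high TA, calmness low TA.

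**Which ten items form each sum.** Two dimensions are named, and four subscales are assigned to their poles. The only ten-item sums that fit are Energy with Tiredness (EA) and Tension with Calmness (TA).

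**EA under the written rule.** EA = Energy + (25 − Tiredness). Leaving wakeful and wide-awake unreversed at this step is right, because they already point towards energy.

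- Fully energetic, not tired: 20 + (25 − 5) = 40.
- Fully tired, not energetic: 5 + (25 − 20) = 10.

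This agrees with the stated poles.

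**TA under the written rule and under the stated poles.** Let T be the Tension sum and C the Calmness sum.

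- Written rule: TA = (25 − T) + C.
- Consistent with the stated poles: TA = T + (25 − C).
- Adding the two: (25 − T + C) + (T + 25 − C) = 50.

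The written score is therefore always 50 minus the intended one. Enumerating all 4^10 response patterns for the ten items confirmed this without exception.

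| Respondent | T | C | TA as written | TA per stated poles |
| --- | --- | --- | --- | --- |
| Most tense, least calm | 20 | 5 | 10 | 40 |
| All Tension items 3, all Calmness items 2 | 15 | 10 | 20 | 30 |
| Least tense, most calm | 5 | 20 | 40 | 10 |

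**Effect on comparisons.** For any two scores a and b, (50 − a) − (50 − b) = −(a − b). Each pre-to-post change and each group difference keeps its size and changes sign. Standard deviations and two-sided p-values stay the same.

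**Sensitivity to the item-direction assumption.** If the item scale ran the other way, so that 4 meant least of the adjective, TA would come out as defined and EA would be inverted. The written rule cannot satisfy both definitions under either item direction.

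**The case against.** The strongest counter-argument is that the composites are inferred: the protocol never says which ten scores are summed or what the sum is called. Tiredness and Tension are also the two subscales that the protocol places in the displeasure quadrants, so reversing exactly those two would orient both sums towards pleasure. That is a coherent coding in itself. It does not rescue the text, because EA and TA are the only dimensions named and the protocol defines TA with tension at the high end. A pleasure-oriented sum would need another name.

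Other points stand as limits on the consequence:

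- The protocol does not say whether five-item or ten-item values are plotted. If only the five-item scores are used, nothing is inverted. The circumplex figure and the AD ACL form are not shown in the text available, so this cannot be settled.
- The AD ACL is given before and after the treadmill test, not during it, and Table 2 does not name it or TA. Its link to the listed affect outcome is through the test battery.
- None of Hypotheses 1 to 4 concerns TA, and the Statistical Analysis Plan section gives a model only for the primary outcome, the relative reinforcing value of physical activity. A dose comparison on TA is possible but is not specified.
- The mirror image is exact, so scores already computed can be recovered as 50 minus the score. An analyst who compares the result with the stated poles might notice the conflict.

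These points bound the damage. None of them reconciles the scoring sentence with the mapping that follows it.

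**Conclusion.** The scoring rule is wrong as written. It contradicts the direction of TA stated in the same section, and following it literally yields 50 minus the intended score on a 10-to-40 scale. This rests on the ten-item TA sum being Tension with Calmness, which the four stated poles imply, and on higher item scores meaning more of the adjective. The consequence, wrong-signed TA results and tense respondents plotted as calm, depends on the ten-item score being used and computed by the written rule.

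The reach is limited to one secondary affect measure and the error can be undone. It should still be corrected, because a sign error that leaves spread and significance intact is easily missed.

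**What to change.** Rewrite the sentence so that it names each sum and its direction:

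- EA = Energy + (25 − Tiredness), higher meaning more energetic.
- TA = Tension + (25 − Calmness), higher meaning more tense.

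Tiredness here is the five-item score with wakeful and wide-awake already reversed within it. State also whether the five-item or the ten-item scores go on the circumplex.

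Bring the scoring code into line and run two test records through it: a fully tense, not calm record must give TA = 40, and a fully calm, not tense record must give TA = 10. Rescore any TA values already produced by the written rule from the item data, or convert them as 50 minus the score.

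The cost is a sentence or two in the protocol and a small change to the scoring. No new data, visits or participants are needed.

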**D. Statistical Analysis Plan**

Differences in groups across time in the primary outcome (RRV_PA_) will be tested using a General Linear Model with treatment group and sex treated as between factors and time (baseline, 6, 10 wk) as a within factor, baseline RRV_PA_ as a covariate and % body fat as a moderator variable. ***Power analysis***: based on demonstrating initial increases in RRV_PA_ of physical activity during the 6 wk treatment period. Assuming α=0.05 and a between-subject SD=8, 15 subjects/group are needed to have 90% power to detect a mean difference in RRV_PA_ of 7 (40% difference) between the 2 levels of physical activity treatment groups at the end of the 6 wk treatment period. Previous studies [[16](#_ENREF_16), [18](#_ENREF_18)] have reported a between subject SD for the RRV_PA_ to range from 35% to 55% of the mean. An SD of 8 represents the midpoint of this range. Therefore, goal recruitment will be 15 subjects per study group.

**E. Anticipated Results and Likely Impact**

We expect that a moderate dose of exercise, a lower intensity of PA exposures, and an interval pattern of exposures will produce greater increases in physical activity reinforcement. The dose prediction is based on findings from the drugs of abuse literature where mid-range doses increase reinforcement more than low or very high doses [[29](#_ENREF_29)]. The objectives of this proposal focus on controlled individual-level treatments to promote healthy choices. Results from this project will inform future community-based behavioral interventions that will provide evidence for guidelines, treatments, and/or tools that can be used by health care providers, policy makers, and stakeholders to help people meet the DGA.

**F. Human Subject Burden (Time, Discomfort, Inconvenience)**

**Table 4.** Time to complete each measurement

|  | # Days assessed | Min to complete/day |
| --- | --- | --- |
| RRV and liking of activity | 3 | 60 |
| Habitual PA | 21 (3 weeks) |  |
| Body composition (DXA) | 2 | 15 |
| Aerobic fitness | 3 | 30 |
| Muscular pain | 3 | 10 |
| Energy/nutrient intake | 12 | 15 |
| Affect | 3 | 30 |
| Exercise questionnaires(6) | 3 | 10 |
| Perceived autonomy support | 1 | 10 |

**G. Requested Subject Reimbursement Schedule(s)**

Reimbursement for the total study is $500/subject or a Choice Health & Fitness membership equivalent to $600/subject.

This will be prorated based on completion of baseline ($150), end of training ($50), and end of follow-up ($300) measures.

**H. Impact on Center Resources**

**i. Budget**

Source of Funds: Center Funds. See budget in **Table 5**.

**Table 5**. *Total project budget*

| item | | | cost, $ | items/subject | Cost/subject, $ | total cost to project, $ (90 subjects) |
| --- | --- | --- | --- | --- | --- | --- |
| Recruitment/ screening |  | | 2000 |  |  | 2,000 |
| Assessments |  | |  |  |  |  |
|  | PA | | 0 | 3 | 0 | 0 |
|  | RRV_PA_ | | 0 | 3 | 0 | 0 |
|  | Questionnaires | | 0 | 19 | 0 | 0 |
|  | DXA | | 10 | 2 | 0 | 0 |
|  | Aerobic fitness | | 10 | 3 | 5 | 450 |
|  | Energy/nutrient intake | | 0 | 12 | 0 | 0 |
|  | Affect test | | 0 | 3 | 0 | 0 |
|  |  | |  |  |  |  |
| Subject stipends |  | | 500 | 1 | 500 | 45,000 |
| Choice Memberships (6 months) | |  | 318 | 1 | 318 | 28,620 |
| Grand Total |  | |  |  |  | 74,070 |

ii.. **Support Staff Time Needed**

*Applied Physiology Laboratory, Nurse Coordinator, and allied staff*:

Recruiting: 90-180 hrs. (1-2 hours per participant)

Screening and consenting: 90 hrs. It is estimated that 1 hrs/participant is needed to screen and consent each

CAReS scheduling: 180 hrs. 2 hours per participant for set-up and maintenance of CAReS throughout the study.

Exercise monitoring: 1440 hrs. It is estimated that on average 24 hr of monitoring will be needed per subject. For 60 participants in exercise groups, 1440 hrs are needed.

Anthropometry (height, weight) - 225 hrs (1 h of direct participant time, 0.5 hr prep and clean-up, 1 hr for data reduction and transfer). For 90 participants, 225 hrs are needed.

Questionnaires – 23.75 hrs (0.25 hr for direct participant time, 1 hr for data reduction and transfer). For 90 participants completing 6 different questionnaires measured on 3 occasions, and one questionnaire measured on one occasion, 23.75 hrs total are needed.

RRV of activity – 607.5 hrs (1.0 h of direct participant time, 0.75 hr preparation and clean-up, 0.5 hr for data reduction and transfer). For 90 participants measured on 3 occasions, 607.5 hrs total are needed.

DXA - 162 hrs (0.3 h for direct participant time, 0.5 hr preparation and clean-up, 1 hr for data reduction and transfer). For 90 participants measured on 3 occasions, 162 hrs total are needed.

Aerobic fitness- 742.5 hrs (1.0 h for direct participant time, 0.75 hr prep and clean-up, 1 hr for data reduction and transfer). For 90 participants measured on 3 occasions, 742.5 hrs total are needed.

*Dietitians:*

Energy intake (food recalls) - 90 hrs; 1.0 hr for reminder calls and checking adequacy of online recalls per participant.

*Statistics:* 24 hrs.

*Information Technology:* 12 hrs. The IT staff estimates 12 hr is needed for CAReS and other data handling.

iii. **Facilities Needed**: This study will utilize mainly the Choice Health and Fitness Laboratory for consenting and volunteer coordination, DXA, fitness measures, phlebotomy, and measures of motivation, and exercise training. The Metabolic Kitchens will be used for meal preparation. Statistical consultation will be provided by [name].

**I. Subject Recruitment Plan.** Participants will be recruited by the Grand Forks Human Nutrition Research Center (GFHNRC) staff using Survey Monkey. Various media will be used to advertise the study. This may include brochures, print media such as the Grand Forks Herald, Dakota Student, Exponent, and Tidbits, television and radio such as the UND television and radio stations. Internet advertisements including University Research Newsletter, University Letter, HEALTHY-UND Listserv, and Work Well Newsletter may be utilized. Recruitment efforts may also include posting flyers around the Greater Grand Forks area, promoting the study at expos and trade shows, and providing information on the GFHNRC website. Recruitment will continue until the study needs are met.

**J. Timetable**. It is anticipated that submission to the Institutional Review Board will be completed by January 13, 2015 for approval on February 6, 2015.

